## Abstract

**Background:**

Surgical site infections (SSI) are the most common health care associated infections in German acute hospitals and can result in prolonged hospital stays, increased use of antibiotics and utilisation of care. *Staphylococcus aureus* bacteria (methicillin-resistant S Aureus (MRSA) and methicillin-susceptible S Aureus (MSSA)) are amongst the most prominent causes of SSI. While up to 90% of documented S Aureus colonization is already detectable prior to hospital admission, the majority of hygiene measures in Germany is focused on the hospital setting. It is hypothesized that early detection and decontamination of S Aureus colonization in primary care can prevent health care associated infections and reduce the number of S Aureus isolates in the hospital setting.

**Methods:**

This study is a controlled interventional study (*N* = 13,260) with a pre-post comparison. The intersectoral intervention (over 2 years) will encompass the following elements: ambulatory detection and decontamination of MRSA and MSSA prior to elective surgery combined with a structured follow-up care. Patients from the control group will be screened in the hospital setting, in accordance with the standard operating procedure (SOP) in routine care. The primary endpoint is the reduction of MRSA and MSSA colonization upon hospital admission. Secondary endpoints are complication rate (SSI), length of stay, recolonization of patients (3 and 6 months after release), patient and provider satisfaction, patient compliance and cost development.

**Discussion:**

In case of positive results, the chance of a widespread uptake and implementation in routine care are considered high. The active involvement of primary care providers in the implementation of screening and decontamination as well as follow-up care is a unique feature of this study. The positive resonance of primary care providers during the recruitment phase highlights the relevance of the topic to the participating actors. These efforts are coupled with patient education and specifically trained medical staff, promising a sustained impact. The STAUfrei care pathway can homogenize current practices in routine care and provide a template for further intersectoral cooperation.

**Trial registration:**

German Clinical Trials Register (DRKS), DRKS00016615. Registered on April 1st, 2019.

## Background

*Staphylococcus aureus* (S Aureus) bacteria are detectable on the skin or mucus membranes of the nasal passage and pharynx in about 20 to 30% of the population [1]. Most of S Aureus isolates exhibit sensitivity to beta-lactam antibiotics (e.g. Methicillin or Oxacillin) and are therefore referred to as methicillin-sensitive S Aureus (MSSA). In contrast, methicillin-resistant S Aureus (MRSA) bacteria are resistant to these antibiotics. MRSA isolates are much rarer than MSSA, only affecting about 1 to 2% of the population in Germany [2].

During surgical interventions both bacterial strains (MSSA and MRSA) can cause infections as they gain access to other organs or tissues. If the infection occurs up to 30 days post-surgery and affects the incision or deep tissue at operating sites they are termed surgical site infections (SSI) [3]. Surgical site infections remain the second most common health-care associated infection (HAI) in Europe and the US [4]. SSIs are associated with prolonged hospital stays, additional physician visits, impairment of the healing process and elevated use of antibiotics [5]. The national guideline by the Robert Koch Institute (RKI) [6] on the prevention of SSI, recommends establishing screening and decontamination procedures for S Aureus, in particular for high risk surgical interventions. While MSSA is increasingly recognized as a risk factor internationally, evidence on the effectiveness of screening and decontamination protocols for MSSA is scarce and it is often not explicitly addressed in national guidelines [5, 6]. Correspondingly, preoperative screening and decontamination efforts in German routine care are targeted at MRSA only. Evidence suggests that decolonization regimes for MSSA can be protective against SSI, particularly since MSSA is a noteworthy contributor to SSI prevalence rates [7, 8].

Unlike for MSSA; the evidence base on MRSA decolonization is more extensive. While the establishment of hospital based screening, isolation and decolonization routines may have contributed to a general decline of MRSA, Germany is still lagging behind when compared internationally [6, 9, 10]. The effectiveness and efficiency of universal screening regimes for MRSA have been documented in several studies, yet screening measures in German routine care are strictly risk based [11–13]. This may result in colonized patients without a corresponding risk profile to remain undetected. Furthermore, decolonization and hygiene measures are commonly implemented during an inpatient hospital stay [7, 11, 12, 14, 15]. With up to 90% of S Aureus cases already being detectable prior to hospital admission [16], shifting screening and decontamination to the primary care setting can provide an effective tool to prevent the introduction of MRSA to the hospital setting. To date only a limited number of studies have assessed the effectiveness of MRSA decontamination regimes in the home environment [14, 17]. Findings point to the importance of patient education and self-sufficiency as integral parts of successful decolonization as direct clinical supervision is lacking in the home setting [14, 17, 18]. Next to that, post-discharge follow-up and decontamination measures can lower the risk of SSIs for MRSA carriers as well as rehospitalisation [19]. In spite of the evidence, the absence of remuneration options has at least partly hampered a systematic prevention and treatment of MRSA colonization and associated complications (SSI) in Germany.

STAUfrei aims to fill these treatment gaps by implementing an intersectoral care pathway stretching from ambulatory screening and decontamination (independent of risk profile) to a structured follow-up care in the primary care setting. Remuneration options for preventative (screening and decontamination) and follow-up (re-)colonization and infection control) care in the outpatient setting is offered by the major health insurance funds in the district. In order to investigate possible advantages of this novel care pathway compared to the current standard operating procedure in routine care, the latter was chosen as a comparison. This is also linked to the overarching aim of a potential nation-wide implementation.

## Methods/design

### Aim

The primary aim of the study is to reduce cases of MRSA and MSSA colonization upon hospital admission. Secondary objectives include prevention of postoperative complications (SSI) and recolonization through a structured follow-up care in the outpatient setting. Additionally, patient compliance, patient and provider satisfaction as well as cost developments will be evaluated.

In order to evaluate the effect of the intervention on a clinical and district level, we aim to carry out a time-series analysis with a pre-post comparison (see Table 1). On a clinical level routine data from the intervention phase (2019–2020) will be contrasted with historic routine data (2015–2018) from the local community hospital. The effect of the intervention will be evaluated both, in terms of clinical and health economic parameters. The district level analysis will be based on routine data from the health insurance fund (AOK Baden-Württemberg). The aim is to evaluate whether the (potential) positive trend in Heidenheim is also observable in other districts. Control districts will be matched according to socioeconomic and demographic aspects (e.g. number and size of hospitals in district, age structure, unemployment rate).

**Table 1 Tab1:** Primary and secondary objectives

Primary research question	
Does the implementation of measures in the primary care setting including ambulatory screening and decontamination reduce MRSA and MSSA colonization rates upon hospital admission?	
Secondary objectives	
Do primary care measures (patient supervision and support through GP practices pre- and post-surgery) reduce recolonization rates (MRSA) amongst patients who underwent elective surgery?	
Does a reduction in MSSA colonization upon hospital admission correlate with an improved quality of care measured by a reduction in surgical site infections, length of stay and rehospitalisation?	
Does the implementation of decontamination measures in the primary care setting lead to a reduction of associated costs for patients undergoing elective surgery?	
How is the feasibility of the intervention evaluated by participating GP practices?	
How do patients evaluate the feasibility of the decontamination in the home environment?	

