**Fig. 1 Fig1:**
[figure not shown]
(A) Evaluation scheme for comparison of control and intervention group from 2019 onwards

**Table 2 Tab2:** (B) Evaluation scheme for time series analysis on clinical (1) and district level (2) from 2015 onwards

	Control phase (Routine care)				Intervention Phase		
	T1 (2015)	T2 (2016)	T3 (2017)	T4 (2018)	T5 (2019)	T6 (2020)	T7 (2021)
(1) Clinical level based on clinical routine data							
Local Clinic	X	X	X	X	X	X	X
(2) District level based on health insurance data							
HDH^a^ District	X	X	X	X	X	X	–
Control District A	X	X	X	X	X	X	–
Control District B	X	X	X	X	X	X	–
Control District C	X	X	X	X	X	X	–

^a^*HDH* Heidenheim

It will not be possible to include the year 2021 in the analysis on district level based on health insurance data (see Table 1). This is due to a time lag in the data delivery of approximately 9 months at the respective insurance fund (time needed for internal quality assurance process).

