##### **(3) Hospital admission** (intervention and control group)

Upon admission all patients scheduled for elective surgery from both control and intervention groups receive a cultural swab of nares, throat and any wounds in order to assess the success of the decontamination (primary endpoint). In case the test result is positive, decontamination measures will be carried out in the hospital setting in accordance with the standard procedure in routine care.

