### Outcomes

Colonization status (MRSA and MSSA) upon hospital admission will serve as the primary endpoint (see Table 3). Secondary endpoints include comparison of length of stay, recolonization and rehospitalisation as well as wound infection rates (SSI). In addition, associated costs of secondary care will be compared. Feasibility of decontamination measures and patient satisfaction with the intervention will be assessed via paper based questionnaires (patients) as well as focus groups (practice teams). In total we aim for 3–4 focus groups with 8–12 participants each. All focus groups will be recorded and subsequently transcribed. As clinical study staff is closely monitoring the implementation at primary care practices and is responsible for the overall project management, 1–2 focus groups with 4–6 participants will be conducted with this particular group. Feasibility of the intervention will also be assessed based on qualitative data (questions from providers and patients to the study coordination office) anonymously collected during the intervention period via the study hotline.

**Table 3 Tab3:** Primary and secondary endpoints, data sources und collection methods

Primary data collection			Routine data collection Heidenheim Clinic	Routine data collection Health insurance data
Patients	GPs, Link Nurses	Clinical data	Clinical data*	Routine data AOK-BW**
• Acceptance / feasibility / satisfaction (QS) • Compliance (QS)	• Acceptance/ feasibility / satisfaction (FG)	• Primary endpoint: Colonization upon hospital admission (MSSA und MRSA) (Lab) • Wound infection rates (SSI) • Recolonization with MRSA 3 + 6 months post-surgery (Lab) • Risk assessment	• MRSA colonization rates (2015–2018) • Length of stay • Rehospitalisation rates • Costs secondary care (incremental cost monitoring)	• MRSA colonization rates (2015 onwards) • Wound infection rates (SSI) • Rehospitalisation rates • Costs primary and secondary care (incremental cost monitoring)

*QS* Questionnaires, *FG* Focus groups, *Lab* Laboratory test result, (A) data for study group comparison (IG vs. CG) and time series analysis* (B) data for time series analysis only**

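### The MRSA colonisation outcome in the time series spans a change in who is swabbed, so the detected rate can move between 2015–2018 and 2019 onwards without any intervention effect

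*Protocol article*

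**What the plan says.** The Aim section fixes the hospital contrast: "On a clinical level routine data from the intervention phase (2019–2020) will be contrasted with historic routine data (2015–2018) from the local community hospital". It adds a district series from the records of one insurer, with control districts matched on socioeconomic and demographic features. Table 2, under Study design, heads 2015–2018 with "Control phase (Routine care").

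The Background says of that routine care that "screening measures in German routine care are strictly risk based", and continues: "This may result in colonized patients without a corresponding risk profile to remain undetected". The intervention pathway, by contrast, tests at the GP practice whatever the risk profile. In step (3) of the patient pathway, "Upon admission all patients scheduled for elective surgery from both control and intervention groups receive a cultural swab of nares, throat and any wounds".

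Table 3 under Outcomes names MRSA colonisation in both routine sources: "MRSA colonization rates (2015–2018") for the hospital and "MRSA colonization rates (2015 onwards") for the insurer. Colonisation on admission during the study is listed separately, as a laboratory result under primary data collection.

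The protocol sets no common screened population for the two periods and no allowance for the number of people tested. The rule that prevalence rests on culture alone deals with false-positive PCR results, not with who is swabbed.

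**The concern.** A detected colonisation rate depends on how many carriers there are and on who is tested. If testing widens on the date the intervention starts, a before-after contrast cannot separate the two.

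The direction depends on the denominator. Per swabbed patient, adding low-risk patients pulls the rate down, which looks like benefit. Per admission or per insured person, finding carriers who used to be missed pushes the rate up, which looks like harm.

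Matching districts does not help. Nothing in the plan changes screening in the control districts, so a shift in testing would appear as an effect specific to Heidenheim. This matters because allocation is not randomised. The Discussion acknowledges selection bias and earlier prevention work at the hospital, and turns to the time series to identify the effects of that earlier work.

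**Working it through.** **The plan's own figure.** No effect size or power is given for the time series. The 92% power with 13,260 patients belongs to the concurrent group comparison. It cannot be reproduced, because the text gives no assumed rates and the group sizes are in a figure that is not shown.

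**Inputs**
- p, true MRSA prevalence: 1–2% (Background, a population figure used here for elective patients).
- f, share of patients swabbed under risk-based screening: assumed 0.2–0.6.
- s, share of all carriers who are among those swabbed: assumed 0.5–0.9, with s > f because risk criteria select carriers.
- Decontamination has no effect, and p is the same in both periods.

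**Formulas, if swabbing goes from risk-based to complete**
- Per swabbed patient: before p·s/f, after p, ratio f/s.
- Per admission: before p·s, after p, ratio 1/s.

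| f | s | Ratio per swabbed patient (f/s) | Ratio per admission (1/s) |
|---|---|---|---|
| 0.2 | 0.9 | 0.22 | 1.11 |
| 0.2 | 0.5 | 0.40 | 2.00 |
| 0.4 | 0.7 | 0.57 | 1.43 |
| 0.6 | 0.9 | 0.67 | 1.11 |
| 0.6 | 0.7 | 0.86 | 1.43 |

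In the middle case at p = 1.5%, the rate per swabbed patient goes from 0.015 × 0.7/0.4 = 2.6% to 1.5%. The rate per admission goes from 0.015 × 0.7 = 1.05% to 1.5%.

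**Same check from stratum prevalences (all assumed).** Let 30% of patients carry a risk factor, with MRSA 3% among them and 0.4% among the rest. Overall prevalence is 0.3 × 3% + 0.7 × 0.4% = 1.18%. Per admission the rate goes from 0.3 × 3% = 0.90% to 1.18% (+31%). Per swabbed patient it goes from 3.0% to 1.18% (−61%). Two other mixes (20% at risk, 3% and 0.6%; 40% at risk, 2.5% and 0.5%) give +80%/−64% and +30%/−48%. The three overall prevalences, 1.08% to 1.30%, lie within the Background's 1–2%.

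**Dilution.** Let w be the share of patients in the series who come under complete swabbing, with the same risk mix as the rest.
- Per admission, the ratio is 1 + w(1/s − 1). The 43% excess at s = 0.7 becomes 43% × w.
- Per swabbed patient, the ratio is (f/s) × [s + w(1−s)]/[f + w(1−f)]. It equals f/s at w = 1 and returns to 1 as w goes to 0.

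The table is therefore the full-coverage extreme.

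**Could it pass for a finding?** Assume 13,260/2 = 6,630 patients a year, four earlier years of the same volume, p = 1.5%, full coverage, and a simple two-proportion test at 0.05 that ignores clustering and serial correlation. At f = 0.4, s = 0.7, the chance of a significant difference with no effect is above 99% per swabbed patient and about 97% per admission. Over the other cases run, it is 39% to nearly 100% per swabbed patient and 23% to nearly 100% per admission.

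**Against the effect sought.** If the 92% applies to MRSA at 0.049 with equal groups, it implies a rate ratio of about 0.50 at a 1% base rate and 0.63 at 2%. The no-effect ratio of 0.57 in the middle case falls between these.

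**After correction.** If both periods use patients screened under the same criteria, s/f is the same in both and the no-effect ratio is 1.00.

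**The case against.** The strongest objection is to the premise. The Background speaks of German routine care in general, and nothing states what the Heidenheim hospital did in 2015–2018. The Discussion says it was already active in prevention. The Abstract describes control patients as screened under the routine-care procedure, while the pathway has every control patient swabbed. Local screening may therefore have been wider than the national picture. This stands: a reader might infer that only risk-flagged patients were swabbed before 2019, but the text supports that only by combining the Table 2 label with the Background.

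A second objection is that denominators and case definitions belong in an analysis plan. This is true of the detail, and Table 3 does not name the source of the hospital MRSA rates after 2018. But the article does fix the periods and the outcome, and neither obvious denominator removes the shift. Only a common screened population does.

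Third, a reader might infer that the whole time series fails, or that the main result is at risk. The documents support neither. Table 3 ranks no outcome in the routine data. Length of stay, rehospitalisation and cost do not depend directly on swabbing. In the primary comparison both groups are swabbed on admission. Secondary analyses are declared not strictly confirmatory. Effects of earlier prevention work can also be looked for within 2015–2018, without crossing the break, although the Aim section uses the series to judge the intervention too, and that does cross it.

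Finally, widened swabbing covers elective study patients of participating insurers and not emergencies, so the shift may be much smaller in wider data. In the district series it also requires that study tests leave a colonisation record with the insurer, which the protocol does not say.

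**Conclusion.** The concern holds for one outcome, MRSA colonisation in the time series. As described, who is tested changes when the intervention starts, so the before-after contrast can shift with no effect. Under the assumed inputs and full coverage, the ratio is 0.22–0.86 per swabbed patient or 1.11–2.00 per admission, and it moves towards 1 as the share of non-study patients grows. The direction is arithmetic. The size rests on the assumed f and s, on the coverage, and on the hospital having screened by risk before 2019. If swabbing there was already universal, the hospital-series shift shrinks, but risk-independent GP testing would still be new to the district series.

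This should be corrected before the series are analysed. It is not critical to the trial: the analysis is supporting and non-confirmatory, and the primary comparison stands.

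**What to change.** 1. State how the hospital screened for MRSA in 2015–2018 and which source supplies the rate from 2019.
2. In the hospital series, restrict both periods to patients screened under the same criteria: those positive on the RKI risk assessment, which the pathway records for all study patients, as far as pre-2019 records allow the same selection. Express the rate per screened patient and print numbers tested beside positives for each year.
3. In the district series, label MRSA colonisation codes descriptive and draw no conclusion on effect from them.
4. Rest any district effect claim on outcomes that depend less on testing, such as rehospitalisation, which Table 3 already lists for the insurer data. SSI is also listed there but needs caution: the follow-up section adds 90-day SSI surveillance for study patients, and nothing extends it to control districts, so its detection may change too.

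The cost is wording in the analysis plan, a filter on the routine data, and fewer patients in the restricted hospital series. If earlier records do not show risk status or who was swabbed, the hospital MRSA series should be descriptive as well.

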### Study design

In order to achieve these objectives the study will employ a controlled study design (A) with a time series analysis (pre-post comparison) on clinic and district level (B) (Fig. 1, Table 2). There is no randomization on practice or patient level. A detailed overview of the endpoints for analysis (A) and (B) can be found in under ‘Outcomes’.

**Fig. 1 Fig1:**
[figure not shown]
(A) Evaluation scheme for comparison of control and intervention group from 2019 onwards

**Table 2 Tab2:** (B) Evaluation scheme for time series analysis on clinical (1) and district level (2) from 2015 onwards

	Control phase (Routine care)				Intervention Phase		
	T1 (2015)	T2 (2016)	T3 (2017)	T4 (2018)	T5 (2019)	T6 (2020)	T7 (2021)
(1) Clinical level based on clinical routine data							
Local Clinic	X	X	X	X	X	X	X
(2) District level based on health insurance data							
HDH^a^ District	X	X	X	X	X	X	–
Control District A	X	X	X	X	X	X	–
Control District B	X	X	X	X	X	X	–
Control District C	X	X	X	X	X	X	–

^a^*HDH* Heidenheim

It will not be possible to include the year 2021 in the analysis on district level based on health insurance data (see Table 1). This is due to a time lag in the data delivery of approximately 9 months at the respective insurance fund (time needed for internal quality assurance process).

### Setting

The study will be carried out in the local clinic in Heidenheim, Baden-Wuerttemberg. Heidenheim has a population of roughly 130,500 inhabitants distributed across elven cities and communities. Being the only hospital in the district, the local community hospital offers treatment to around 90% of local inpatient cases. The largest health insurance companies in the Heidenheim district are the AOK Baden Württemberg (Allgemeine Ortskrankenkasse), AOK-Bayern, BKK (Betriebskrankenkasse) and the IKK (Innungskrankenkasse). All have signed selective agreements (§140SGBV) with the local community hospital allowing the majority of the local population to partake in the study.

